#### **7.5     *Management of adverse events***

Management of AEs is generally achieved by dose reduction (see Table 4); however, in the case of life-threatening adverse events, identification of cardiac disease or development of cardiac dysfunction, pregnancy, failure to comply with the requirement for the practice of birth control for both male and female patients, both PegIntron® and Rebetol® therapy should be discontinued permanently.

Upon complete recovery of the adverse event, treatment with interferon alfa-2b and ribavirin may be resumed at a dose that is 50% lower than the dose associated with the adverse event. If this dose is tolerated for at least two weeks, treatment may be resumed at the dose associated with the adverse event. If the adverse event recurs, a reduced, tolerated dose may be administered and maintained or the subject may be taken off the treatment optimization study at the physician's discretion. If a dose reduction is necessary because of an adverse event, the patient must be examined every 2 weeks.

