The daily dose is reduced if indirect bilirubin again rises above 4 mg/dl. This dose is then maintained. Treatment may be continued only if indirect bilirubin remains below 2.5 mg/dl. If indirect bilirubin remains high (> 4 mg/dl for more than 4 weeks), PEG-interferon alfa-2b and ribavirin must be permanently discontinued.

If an adverse laboratory event persists that is not severe enough to mandate permanent discontinuation of the drugs, the reduced dose of PEG-interferon alfa-2b or ribavirin (whichever was reduced) may be maintained. If the ribavirin dose was reduced following a decline in hemoglobin to below 10 g/dl, the dose reduction must continue to apply for at least 4 weeks.

The reduced doses may also be maintained if the hemoglobin value is  $\geq 12$  g/dl for women and  $\geq 13$  g/dl for men. If the adverse laboratory event recurs, a reduced, previously tolerated dose may be administered and maintained or the subject may be taken off the treatment optimization study at the physician's discretion.

The dose reduction takes place by lowering the PEG-interferon alfa-2b injection volume and number of ribavirin capsules as described in the tables below. Subjects who develop life-threatening adverse events must have PEG-interferon alfa-2b and ribavirin discontinued definitely.

To ensure that daily dosing is maintained, the dose should be reduced, not the frequency of use.

Table 5: Reduction of Rebetol®

| Initial ribavirin dose | Total number of capsules per day | Reduced dose | Reduced number of capsules per day |
|------------------------|----------------------------------|--------------|------------------------------------|
| 1400 mg/day            | 3-0-4                            | 800 mg/day   | 2-0-2                              |
| 1200 mg/day            | 3-0-3                            | 800 mg/day   | 2-0-2                              |
| 1000 mg/day            | 2-0-3                            | 800 mg/day   | 2-0-2                              |
| 800 mg/day             | 2-0-2                            | 600 mg/day   | 1-0-2                              |

Table 6: Reduction of PegIntron®

| Current dose   | Next dose reduction |
|----------------|---------------------|
| 150 µg         | 120 µg              |
| 135 µg, 120 µg | 100 µg              |
| 105 µg, 100 µg | 80 µg               |
| 90 µg, 80 µg   | 50 µg               |
| 70 µg, 60 µg   | 30 µg               |

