## 8 STATISTICAL METHODS AND SAMPLE SIZE

### 8.1 *Statistical Methods*

The primary statistical analysis will be the comparison of rates for SVR in the ITT population (all randomized patients who received at least one PEG-Interferon injection) in the group with a prolongation of treatment by 24 weeks and a total treatment duration of 48 weeks (Group A) in comparison with the SVR rates in patients without treatment prolongation. The SVR rates of the latter group are assumed to be  $\pi_0=70\%$  from historical data. According to the study design and the main objective, a one-sided test for proportions with a significance level of  $\alpha=5\%$  will be used to test the following hypothesis:

$$H_0: \pi_0 = \pi_{24 \text{ ext}} \text{ versus } H_1: \pi_0 \leq \pi_{24 \text{ ext}}$$

As main secondary statistical analysis, an analogous test is performed for Group B (treatment prolongation by 12 weeks for a total treatment duration of 36 weeks), again with a significance level of  $\alpha=5\%$ .

$$H_0: \pi_0 = \pi_{12 \text{ ext}} \text{ versus } H_1: \pi_0 \leq \pi_{12 \text{ ext}}$$

As further secondary statistical analysis, a comparison of SVR rates of Group A and Group B is planned, testing the one-sided hypothesis

$$H_0: \pi_{12 \text{ ext}} = \pi_{24 \text{ ext}} \text{ versus } H_1: \pi_{12 \text{ ext}} \leq \pi_{24 \text{ ext}}.$$

Further explorative analysis are planned to compare clinical variables and secondary end points between Group A (48 weeks) and B (36 weeks) with appropriate statistical methods as, e.g., Fishers exact test,  $\chi^2$  test, t-test, Mann-Whitney U test and corresponding confidence intervals will be used. Typically, tests will use a significance level of  $\alpha=5\%$  and can be one- or two-sided. Further explorative statistical analysis, e.g., the analysis of predictors for SVR may be used if appropriate.

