### **12.1 Procedures for handling patients lost to follow-up and drop-outs**

Investigators should make an attempt to contact those patients who do not return for scheduled visits or follow-up. Information gathered should be described on the Study Conclusion page of the Case Report Form and on Medication/Adverse event forms.

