### **12.2 Reasons for drop-out**

It should be specified on the Study Conclusion page of the case report form which of the following possible reasons were responsible for drop-out of the patient from the study:

- Serious adverse event
- Non-serious adverse event
- Protocol violation (specify)
- Consent withdrawal, not due to an adverse event
- Migration from the study area
- Lost to follow-up
- Other (specify)

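### A patient with a recurrent adverse event may be taken off the study, and nothing in the protocol secures the FU24 HCV-RNA sample that the ITT SVR analysis needs

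*Protocol*

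**What the plan says.** Protocol 7.5 gives the physician two options when an adverse event recurs: the patient is kept on a reduced, tolerated dose, or "the subject may be taken off the treatment optimization study", at the physician's discretion. The General Remarks in the same section repeat this for laboratory events: "a reduced, previously tolerated dose may be administered and maintained or the subject may be taken off the treatment optimization study".

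For other triggers, such as life-threatening events, 7.5 speaks of the drugs only: "therapy should be discontinued permanently". So the section has separate wording for stopping treatment and for leaving the study.

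Protocol 12.2 asks which reasons were "responsible for drop-out of the patient from the study". The list holds serious and non-serious adverse events beside withdrawal of consent and loss to follow-up. It has no entry for a patient who stops drug but stays in follow-up.

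On retrieval, 12.1 says: "Investigators should make an attempt to contact those patients who do not return for scheduled visits or follow-up". Section 13.3 asks for efforts to document the outcome after withdrawal for a treatment-limiting adverse event. Neither names an HCV-RNA sample.

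The endpoint in 3.2 is HCV-RNA 24 weeks after the end of treatment. The ITT population in 8.1 is "all randomized patients who received at least one PEG-Interferon injection", so a removed patient who has been dosed stays in the denominator. The power statement in 8.2 needs ITT information on 75 patients per group, which is exactly the number randomised to each group in 3.3.

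**The concern.** A site that follows 7.5 literally may end a patient's participation for a recurrent, less severe event, although more dangerous events end only the drugs. Once the patient is off the study, nothing obliges the site to take the FU24 sample. The patient still counts in the ITT population, but the primary outcome is unknown.

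Many of these patients could have a favourable outcome. They enter after about 24 weeks of therapy, and the pooled historical row in 8.3 shows 93/151 (61.6%) SVR on 24 weeks without RVR. If their missing results count as failures, SVR is understated. If they are excluded, SVR tends to be overstated, because those removed probably do worse than those who stay.

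Group A takes study drug for 24 weeks and Group B for 12, and the trial is open label. Group A patients have longer to meet the rule, and the physician knows the arm when deciding. Loss may therefore be greater in Group A, which would distort the comparison of the two extensions that section 2 names as the objective.

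**Working it through.** **Inputs from the protocol.** 75 patients per group (3.3, 8.2); one-sided α = 5%; reference rate 70%; assumed SVR 95% in A and 85% in B (8.2).

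**Assumed inputs.** The fractions lost, d_A and d_B, since the protocol gives none; 60% SVR in those removed (rounded from 61.6% in 8.3); missing counted as failure.

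**Step 1: the plan's own figures.**
- Each group against 70%: the smallest count of 75 with exact one-sided error at or below 5% is 60 (exact error 3.5%). P(X ≥ 60) is 91.1% at SVR 85% and above 99.9% at 95%. The plan states at least 90% and nearly 100%.
- A versus B, continuity-corrected: power = Φ[(p_A − p_B − 1/75 − 1.645·s0)/s1]. Here s0 = √(2·p̄(1 − p̄)/75), with p̄ the mean of the two rates, and s1 = √(p_A(1 − p_A)/75 + p_B(1 − p_B)/75). With 0.95 and 0.85, s0 = 0.0490 and s1 = 0.0483. The argument is (0.10 − 0.0133 − 0.0806)/0.0483 = 0.126, so power is 55.0%. The plan states 55%.

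All three reproduce.

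**Step 2: effect of loss with missing = failure.** Each removed patient who would have reached SVR is scored as a failure, so observed SVR = planned SVR − 0.60·d.

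| Lost A / B | Observed SVR A | Observed SVR B | Difference (points) | A vs B power | B vs 70% power | A vs 70% power (primary) |
|---|---|---|---|---|---|---|
| 0 / 0 | 95% | 85% | 10 | 55% | 91% | >99.9% |
| 5% / 2.5% | 0.95 − 0.03 = 92% | 0.85 − 0.015 = 83.5% | 8.5 | 38% | 84% | >99.9% |
| 10% / 5% | 0.95 − 0.06 = 89% | 0.85 − 0.03 = 82% | 7 | 25% | 73% | 99.3% |

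**Step 3: range over which this is possible.** Patients who stay cannot exceed 100% SVR, so in Group A (0.95 − 0.60·d)/(1 − d) ≤ 1. This gives 0.40·d ≤ 0.05, or d ≤ 12.5%. At 5% loss those who stay need 0.92/0.95 = 96.8%. At 10% they need 0.89/0.90 = 98.9%, which is close to the ceiling. At 15% they would need 0.86/0.85 = 101%, which is impossible.

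**Step 4: exclusion instead.** Suppose true SVR in Group A is 70%, so the null holds, and 10% are lost, leaving about 68 patients. If SVR in the lost is 50%, SVR in those who stay is (0.70 − 0.05)/0.90 = 72.2%. If it is 30%, it is (0.70 − 0.03)/0.90 = 74.4%. The exact cut-off for 68 patients is 55. The false-positive chance on the primary test is then 6.9% and 13.9%, against a nominal 5%.

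**The case against.** The strongest reply is that little is likely to be lost. The option is narrow: the event must recur, removal is discretionary, and a reduced dose is the stated alternative. Patients are already selected for tolerance, because 4.3 excludes adherence below 80% up to randomisation. Both groups have 24 weeks of follow-up in 3.1, the endpoint runs from the end of treatment, and HCV-RNA is scheduled at FU4, FU12 and FU24. Sections 12.1 and 13.3 add contact attempts and documentation of the outcome. Handling of missing results may also be settled in an analysis plan that is not at hand.

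Much of this stands as a limit on size. The loss rates used here are assumptions, and loss could be small. The direction of bias does depend on the missing-data rule. But no section says that the follow-up schedule applies to a patient taken off the study. A contact attempt is not a sample, and an analysis rule cannot supply a result that was never collected.

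A reader might infer that Group A will certainly lose more patients. The protocol does not show this: it is an inference from twice the on-study exposure and the open-label design. A reader might also infer that the primary conclusion is endangered. Under missing = failure it hardly is, since Group A versus 70% keeps about 99% power at 10% loss.

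**Conclusion.** The point holds as a gap in data collection. Sections 7.5 and 12.2 mix stopping drug with leaving the study, and nothing secures FU24 HCV-RNA for patients removed after an adverse event, although 8.2 allows for no loss.

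Under missing = failure, the cost falls on the main secondary test and on the randomised comparison. Group B versus 70% drops from 91% to about 84% or 73%, and A versus B from 55% to about 38% or 25%, at assumed losses of 5%/2.5% or 10%/5%. These figures rest on the assumed loss rates, on 60% SVR in those removed, and on 95% and 85% as the true ITT rates. Heavier losses, such as 15% in Group A, should not be used as an illustration, because they are not attainable with these inputs.

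If missing results were excluded, the primary test would be exposed to an inflated false-positive rate, but the protocol does not say that they will be. This is a cheap improvement worth making, not a fault that invalidates the primary analysis.

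**What to change.** Leave the clinical rules in 7.5 as they are. Add one data-collection sentence, for example in 12.1 with a pointer from both places in 7.5: any randomised and dosed patient who stops study drug, or is taken off under 7.5, is asked, unless consent is withdrawn, to give the end-of-treatment sample and the FU4, FU12 and FU24 HCV-RNA samples, counted from the last dose.

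In 12.2, record the reason for stopping treatment separately from the reason for leaving follow-up.

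The cost is amendment wording and one CRF page. The visits and HCV-RNA tests are already in the schedule in 5.1. The downside is a few follow-up visits in patients who would otherwise have left.

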### **General Remarks**

Unscheduled visits may take place for evaluation of laboratory parameters relevant to clinical safety. An unscheduled visit to monitor hemoglobin will be performed within one week of the patient's last visit if the patient displays a hemoglobin decline which meets all of the following three criteria:

- ⇒ Decline in hemoglobin since the previous visit
- ⇒ Decline in hemoglobin by more than 2 g/dl since the baseline evaluation
- ⇒ Decline in hemoglobin below 11 g/dl.

At the physician's discretion, the patient or a household member will be trained in the subcutaneous injection technique.

Table 4: Rules for dose reductions of PegIntron® and Rebetol®

|                        | Dose reduction                              | Permanent discontinuation of treatment        |
|------------------------|---------------------------------------------|-----------------------------------------------|
| HEMOGLOBIN             | < 10 g/dl
(Rebetol®)                     | < 8.5 g/dl
(Rebetol®)                      |
| WHITE BLOOD CELL (WBC) | < 1.5 X 10  /l
(PegIntron®)  | < 1.0 X 10  /l
(PegIntron®)    |
| GRANULOCYTE            | < 0.75 X 10  /l
(PegIntron®) | < 0.5 X 10  /l
(PegIntron®)    |
| PLATELET               | < 50 X 10  /l
(PegIntron®)   | < 30 X 10  /l
(PegIntron®)     |
| CREATININE             | n/a                                         | > 3.0 mg/dl                                   |
| ALT/AST                | n/a                                         | 2 x baseline and >10 x ULN                    |
| BILIRUBIN-INDIRECT     | > 5 mg/dl (or > 85.5 µmol/l)*
(Rebetol®) | > 4mg/dl (or >68.4 umol/l)
(for > 4 weeks) |
| BILIRUBIN-DIRECT       |                                             | > 2.5 x ULN                                   |

\* Discontinue ribavirin alone for at least 1 week and no more than 2 weeks. Also take a blood sample to determine clotting. If indirect bilirubin falls to < 2.5 mg/dl after ribavirin treatment is interrupted, ribavirin treatment may be restarted at the nearest reduced daily dose stated in the protocol. If bilirubin remains stable at values below 2.5 mg/dl for a period of 4 weeks, ribavirin treatment may be resumed at the full (100%) protocol dose.

The daily dose is reduced if indirect bilirubin again rises above 4 mg/dl. This dose is then maintained. Treatment may be continued only if indirect bilirubin remains below 2.5 mg/dl. If indirect bilirubin remains high (> 4 mg/dl for more than 4 weeks), PEG-interferon alfa-2b and ribavirin must be permanently discontinued.

If an adverse laboratory event persists that is not severe enough to mandate permanent discontinuation of the drugs, the reduced dose of PEG-interferon alfa-2b or ribavirin (whichever was reduced) may be maintained. If the ribavirin dose was reduced following a decline in hemoglobin to below 10 g/dl, the dose reduction must continue to apply for at least 4 weeks.

The reduced doses may also be maintained if the hemoglobin value is  $\geq 12$  g/dl for women and  $\geq 13$  g/dl for men. If the adverse laboratory event recurs, a reduced, previously tolerated dose may be administered and maintained or the subject may be taken off the treatment optimization study at the physician's discretion.

The dose reduction takes place by lowering the PEG-interferon alfa-2b injection volume and number of ribavirin capsules as described in the tables below. Subjects who develop life-threatening adverse events must have PEG-interferon alfa-2b and ribavirin discontinued definitely.

To ensure that daily dosing is maintained, the dose should be reduced, not the frequency of use.

Table 5: Reduction of Rebetol®

| Initial ribavirin dose | Total number of capsules per day | Reduced dose | Reduced number of capsules per day |
|------------------------|----------------------------------|--------------|------------------------------------|
| 1400 mg/day            | 3-0-4                            | 800 mg/day   | 2-0-2                              |
| 1200 mg/day            | 3-0-3                            | 800 mg/day   | 2-0-2                              |
| 1000 mg/day            | 2-0-3                            | 800 mg/day   | 2-0-2                              |
| 800 mg/day             | 2-0-2                            | 600 mg/day   | 1-0-2                              |

Table 6: Reduction of PegIntron®

| Current dose   | Next dose reduction |
|----------------|---------------------|
| 150 µg         | 120 µg              |
| 135 µg, 120 µg | 100 µg              |
| 105 µg, 100 µg | 80 µg               |
| 90 µg, 80 µg   | 50 µg               |
| 70 µg, 60 µg   | 30 µg               |

## 7.6 *Benefit-Risk-Assessment*

The optimal treatment duration for patients without RVR is not known until now. While some patients may be treated for a shorter period of time to reduce costs and side-effects, others may need longer treatment to improve the response rates. In this study we intend to treat patients with chronic hepatitis C of genotype 2 or 3 having characteristics associated with poor treatment response for additional 12 or 24 weeks beyond the standard treatment of PEG-IFN alpha-2b plus ribavirin to obtain data for a possible therapy-optimisation. Patients may profit of a prolonged treatment i.e. higher chances for permanent cure. Since not all participating patients will benefit from the therapy immediately, a direct benefit may not be seen for each individual (see Chapter 1). No evidence is available at the time of the completion of the study protocol to the Hep-Net Study Group indicating that a prolonged

intake of the study medication may need special warnings or precautions, other than those noted in the SmPC. Since all participating patients will have to be treated with the study medication for 24 weeks prior to entering the study, the individual adverse drug reaction profile will be well known to the patient and investigator.

Possible risks of PegIntron® include flu-like symptoms, fever, chills, fatigue and malaise two to eight hours after the initial dose. The initial reactions are usually mild to moderate. Tachyphylaxis may occur after 3-5 doses. Patients may take acetaminophen one hour before administration of PegIntron® and every 4 hours thereafter until the flu-like symptoms resolve. Changes of blood-picture are well known (see above) as well as a depression may occur. Further details are described in the SmPC.

Possible risks of Ribavirin® include changes of the blood-picture, especially anaemia (see above). Also itching and rashes are well known. Rare cases include insomnia and cough and increased levels of uric acid.

Animal experiments showed that administration of ribavirin to pregnant experimental animals sometimes resulted in the death of an embryo or caused congenital abnormalities in some of the offspring. There is no clinical data to demonstrate potentially harmful effects on unborn children, but it is assumed that the effects in human subjects would be similar to those seen in animal experiments. Animal studies also show that sperm morphology (structure) changes during ribavirin treatment. Ribavirin may persist in sperm fluid for two sperm generations. Therefore, men must also practice contraception during treatment and for 7 months after discontinuing ribavirin. Further details are described in the SmPC.

The fatigue typical of the first few weeks of interferon treatment may be more frequent or severe when ribavirin is added to the PEG-Interferon alfa-2b regimen. Therefore, patients on this combination should exercise caution and avoid driving motor vehicles or operating machinery, or consult their physician before driving a car or other vehicles or operating power tools or machinery.

## 8 STATISTICAL METHODS AND SAMPLE SIZE

### 8.1 *Statistical Methods*

The primary statistical analysis will be the comparison of rates for SVR in the ITT population (all randomized patients who received at least one PEG-Interferon injection) in the group with a prolongation of treatment by 24 weeks and a total treatment duration of 48 weeks (Group A) in comparison with the SVR rates in patients without treatment prolongation. The SVR rates of the latter group are assumed to be  $\pi_0=70\%$  from historical data. According to the study design and the main objective, a one-sided test for proportions with a significance level of  $\alpha=5\%$  will be used to test the following hypothesis:

$$H_0: \pi_0 = \pi_{24 \text{ ext}} \text{ versus } H_1: \pi_0 \leq \pi_{24 \text{ ext}}$$

As main secondary statistical analysis, an analogous test is performed for Group B (treatment prolongation by 12 weeks for a total treatment duration of 36 weeks), again with a significance level of  $\alpha=5\%$ .

$$H_0: \pi_0 = \pi_{12 \text{ ext}} \text{ versus } H_1: \pi_0 \leq \pi_{12 \text{ ext}}$$

As further secondary statistical analysis, a comparison of SVR rates of Group A and Group B is planned, testing the one-sided hypothesis

$$H_0: \pi_{12 \text{ ext}} = \pi_{24 \text{ ext}} \text{ versus } H_1: \pi_{12 \text{ ext}} \leq \pi_{24 \text{ ext}}.$$

Further explorative analysis are planned to compare clinical variables and secondary end points between Group A (48 weeks) and B (36 weeks) with appropriate statistical methods as, e.g., Fishers exact test,  $\chi^2$  test, t-test, Mann-Whitney U test and corresponding confidence intervals will be used. Typically, tests will use a significance level of  $\alpha=5\%$  and can be one- or two-sided. Further explorative statistical analysis, e.g., the analysis of predictors for SVR may be used if appropriate.

